### Methods

To attain these two aims, we propose to use the following methodological strategy:We will obtain population-level data on abortion care seeking (method, provider, setting and post-abortion symptoms and care-seeking) in two sites in Kenya and Burkina Faso where access to legal abortion services is highly restricted, by applying Anonymous Third Party Reporting (ATPR) (also known as confidantes’ method) and Respondent-Driven Sampling, both modified with features that can potentially improve their implementation or accuracy.We will modify the Anonymous Third Party Reporting (ATPR) method by refining and validating the method for future use in large scale surveys by: 2a. developing a formative study to determine whether the ATPR is pertinent in that context; 2b. identifying the best network-generating question; 2c. measuring the size of the two biases (barrier and transmission) which affects its estimates using data generated by RDS and self-report, and if pertinent, correct the ATPR estimates using the generalized Network Scale-Up Method (NSUM) model, correct also for selection bias; 2d. assessing the potential for self-report data and stigma data to help in yielding ATPR bias estimates in different contexts; 2d. conducting internal validation for the ATPR using known quantities; 2e. comparing ATPR safety estimates with those from RDS.We plan to improve on RDS for abortion by 3a. testing a multiplex design; 3b. obtaining a large sample of abortion seekers and reaching equilibrium.

### Study setting and population

The study will be conducted in two Health and Demographic Surveillance Systems (HDSS), the Nairobi HDSS in Kenya [42] and the Kaya HDSS in Burkina Faso [43]. In both countries, induced abortion is allowed on narrow grounds. In Burkina Faso, abortion is allowed on the grounds of rape, incest, fetal impairment, saving the woman’s life and health. In Kenya, abortion is legal if it is performed to protect the women’s health or if the pregnancy is life-threatening or the pregnant women’s life is otherwise endangered.

HDSS track a population and its vital events (e.g. births, deaths, migration) in a given catchment area, which often corresponds to a health district [42–44]. Once a surveillance area has been delineated, a census is undertaken; fieldworkers then visit each household at least once a year to update the household roosters. They document all in-migrations, out-migrations, deaths and births which occurred in the households since the last round. HDSS have been especially useful to study causes of deaths [44]; they also host clinical trials, and epidemiological or demographic studies.

HDSS offers several advantages to study abortion safety at the population level in contexts where access to abortion services is highly restricted: (1) the RDS needs to be applied at a local scale; (2) these two HDSS are run by Human Reproduction Programme Long term Institutional Development Hubs (HRP LID—HUBS) in sub-Saharan Africa (African Population Health Research Center, APHRC, in Kenya and Institut de Recherche en Sciences de la Santé, IRSS, in Burkina Faso), two institutions which have high research and dissemination capacities (both research dissemination and institutional experience with community-based work), key aspects for an innovative project on a sensitive topic. This choice allows us to strengthen research capacity, with the aim of having HRP LID-HUBS researchers using, advancing and disseminating state-of-the art network-based survey methods for sensitive behaviours and abortion research in other highly restrictive settings.

The systematic review [20] confirms that both sites meet the criteria for network-based approaches (abortion services cannot be accessed anonymously: low transmission bias among close relations). These two sites also represent some of the diversity of sub-Saharan Africa (from rural to small town in Kaya to large city in Nairobi, in West and East Africa). Validating network-based approaches in rural, small town and large city settings is a necessity, as dynamics of social relations and disclosure are likely to vary across types of residence.

### Overall study design: two phases

The two HDSS sites will obtain approvals from their local institutional review boards prior to the start of the project. The project is divided into two phases (Table 2). In a first phase, each HDSS will conduct a formative research, where the existence of the transmission bias will be probed in a qualitative study and the other biases will be investigated by conducting a quantitative pre-test for the ATPR and for the RDS. The study will then move to phase 2 (main survey: ATPR and RDS) if the data collected during phase 1 shows that the ATPR and RDS can be implemented for abortion in that site. For RDS, this means that phase 1 can produce at least 6 seeds that can successfully recruit 30 respondents. For ATPR this means that abortion rate obtained fall within in a plausible range.

**Table 2 Tab2:** Study design

	Within HDSS	Outside HDSS	
Phase 1: Formative research	Qualitative study n = 20 in-depth interviews	Pre-test ATPR n = 100	Pre-test RDS n = 30
Phase 2: Main survey	ATPR n = 2000 Cross-sectional random survey collecting retrospective information (last 3 years) on abortion of close relations and on respondents' abortions		
	RDS n = 500 Prospective data collection with women who had abortion last 3 years (or individuals close to an abortion seeker)		

#### Phase 1: Formative study: qualitative study and pre-tests for ATPR and RDS

In phase 1, each HDSS will conduct a qualitative study (in the HDSS area) and pre-test the ATPR and RDS instruments and procedures in two different locations both outside of the HDSS area.

##### Qualitative study

The qualitative study will produce contextual knowledge on the practice of abortion, the circulation of information on abortion and abortion stigma, with the aim of testing whether the basic condition for ATPR / RDS use for abortion (low transmission bias among close relations) is met. The qualitative study could in addition provide a number of seeds for the main RDS survey. The qualitative material will also attune us to local terms used for abortion, diversity of methods used locally, etc., which will help ensure the translations of the questionnaires are correct and that response categories are pertinent. To this end, 20 in-depth interviews (IDI) will be conducted with a diversity of women living in the area willing to talk about women’s health problems, and referred by key informants in the community. This low number was deemed enough as several qualitative studies on the same topic have already been conducted in these countries showing that transmission bias for abortion is low among close relations; these IDI are thus confirmatory for the study sites. Informed consent will be sought and privacy ensured. The topics to be discussed in the IDI will include: (i) features of close female networks; (ii) the difficulties involved in deciding what to do when faced with an unplanned pregnancy, accessing abortion services, dealing with complications; how networks are involved in these various steps; (iii) social perceptions of and stigma surrounding abortion. The exact direction and content of discussions will be determined by participants. IDI will be recorded, translated (in French or English) and transcribed.

##### Pre-tests of the ATPR and RDS

In a location outside of the HDSS area (but similar in features), the questionnaire for the ATPR will be tested on 100 women aged 15–49. The questionnaire will include two successive network generator questions (the internationally validated “people you have discussed important matters with during the past year” as well as “up to three women you share secrets with”). The test of ATPR will advance knowledge on the network generating question best suited to investigate abortion and verify that the different biases (transmission, barrier, selection, social desirability) do not preclude the collection of data on abortion. The RDS pre-test will be conducted in a second location, also outside of the HDSS area, but also similar. The aim of the pre-test for the RDS is to fine-tune the RDS procedures (seeds, location for the interviews, etc.) and ascertain that abortion seekers in the study context accept to conduct interviews following peer-referral and to disclose their abortion in that context. Women recruited from 6 seeds following the RDS procedure (see more below) will be interviewed (up to a maximum of 30 individuals or 2 months of efforts). Among the six, three multiplex seed will be tested, in which respondents will be asked not only to recruit another abortion seeker but can also recruit somebody who knows an abortion seeker.

#### Phase 2: Main survey

In each site, the two components of the study will be conducted one after the other in the HDSS area. The ATPR will be run first and respondents will be warned about the coming RDS survey; they will be offered a coupon, to give the relation or fieldworker in case they are approached for the RDS. The RDS will start as soon as the ATPR stops. In the Kaya HDSS, three sub-geographies will be considered, distinguishing the rural part under surveillance from the urban part itself comprising of both formal and informal settlements. The goal is to make sure the ATPR sample is representative of all sub-geographies (that the sampling frame is complete for all areas, which necessitates extra work for informal areas) and that RDS seeds are diversified from that point of view.

### Data collection: Anonymous Third Party Reporting method

#### Sampling, inclusion criteria, and interview setting

We will conduct a cross sectional representative household-based survey among women aged 15–49. We will draw a simple random sample from the sampling frame of women 15–49 usually residing in the HDSS and randomization tables. We will use Excel to generate random numbers that will be apply to the ordered list of women in the area. The definition of residence may vary slightly across sites. To calculate sample size, we used estimates of abortion rates from published numbers in national studies or global estimates; numbers indicate a low 22 abortions per 1000 women aged 15–49 in rural Burkina Faso to a high of 48 abortions for 1000 15–49 in Kenya. The number of women aged 15–49 living in the HDSS area varies from 8500 in Nairobi to 10,000 in Kaya. Using these inputs and a random sample design, we determined that 1500 women in each site were enough to yield reliable abortion safety estimates across the two sites, assuming a reporting rate of 50% (one in two women knowing about the abortion of their close relation will report it in the survey) and two close relations. Along these assumptions, we will collect data on about 150 abortions in Kaya, and the double in Nairobi. To anticipate on possibly lower reporting rates and number of relations or abortion rates, we increase the sample size to 2000 in each site. All women^6^ who consent to participate in the study will be interviewed using the self-report/ATPR tool, in a private setting in their home or close surroundings, face to face by an interviewer recording answers on tablets.

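### The ATPR yield of about 150 abortions in Kaya and double in Nairobi does not follow from the listed inputs, which give about 99 and 216 at 1,500 women and 132 and 288 at 2,000

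*Protocol article*

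**What the plan says.** The sizing of the ATPR survey is in the protocol article under *Sampling, inclusion criteria, and interview setting*. It takes abortion rates of 22 per 1,000 women of reproductive age for rural Burkina Faso and 48 per 1,000 for Kenya. On sample size it states "we determined that 1500 women in each site were enough to yield reliable abortion safety estimates across the two sites". Behind this stand two further inputs: each respondent has two close relations, and half of the respondents who know of a relation's abortion disclose it to the interviewer. The expected yield is given next: "Along these assumptions, we will collect data on about 150 abortions in Kaya, and the double in Nairobi". As cover for lower reporting, fewer relations or lower abortion rates, the authors then write "we increase the sample size to 2000 in each site".

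That paragraph gives neither a recall window nor a time unit for the rates. The window is in Table 2 under *Overall study design: two phases* ("Cross-sectional random survey collecting retrospective information (last 3 years") and again in the ATPR *Questionnaire* section. Table 2 and the questionnaire also show that respondents are asked about their own abortions.

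**The concern.** The sentence giving the yield presents it as the result of the assumptions just listed, so a reader should be able to multiply them out and arrive at about 150 and 300. The product is clearly lower in both sites.

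This count is the only quantitative support for the statement that 1,500 women are enough. It is also the benchmark against which the increase to 2,000 is offered as cover for worse inputs. If the listed inputs already give fewer than 150 and 300 at 2,000, a reader who relies on that benchmark expects more abortions, and a little more precision in the safety shares, than the plan's own assumptions deliver.

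**Working it through.** **Inputs**

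- Women per site: 1,500, then 2,000 (*Sampling, inclusion criteria, and interview setting*).
- Close relations per respondent: 2 (same section).
- Reporting rate: 0.5, defined for abortions of close relations (same section).
- Abortion rate: 0.022 in Kaya and 0.048 in Nairobi (same section). No time unit is given; annual is assumed here.
- Window: 3 years (Table 2 and the ATPR *Questionnaire* section).

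**Formula.** The article shows none. The natural one is: yield = women × relations × annual rate × years × reporting rate.

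**Attempt to reproduce the stated yield at 1,500 women**

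- Kaya: 1,500 × 2 × 0.022 × 3 × 0.5 = 99, against about 150. Shortfall (150 − 99)/150 = 34%.
- Nairobi: 1,500 × 2 × 0.048 × 3 × 0.5 = 216, against about 300. Shortfall (300 − 216)/300 = 28%.

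The stated yield is not reproduced.

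**At the planned 2,000 women**

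- Kaya: 2,000 × 2 × 0.022 × 3 × 0.5 = 132, which is 12% below 150.
- Nairobi: 2,000 × 2 × 0.048 × 3 × 0.5 = 288, which is 4% below 300.

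Reaching the stated figures on these inputs needs 150/0.066 ≈ 2,273 women in Kaya and 300/0.144 ≈ 2,084 in Nairobi.

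**Could another reading give 150 and 300 at 1,500 women?**

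| Reading | Kaya | Nairobi |
|---|---|---|
| Two relations, 1 year, 50% | 33 | 72 |
| Two relations, 5 years, 50% | 165 | 360 |
| Two relations, 3 years, 100% | 198 | 432 |
| Two relations at 50% plus own abortions at 100%, 3 years | 198 | 432 |
| Three women per respondent, 3 years, 50% | 148.5 | 324 |

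Only the last comes close. It matches Kaya and overshoots Nairobi by 8%; the ratio 48/22 = 2.18 fits a loose doubling. At 2,000 women it gives 198 and 432.

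With two relations, 150 in Kaya would need a rate of 33.3 per 1,000 or 76% reporting. In Nairobi, 300 would need 66.7 per 1,000, above the stated high of 48, or 69% reporting.

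**Effect on precision.** The 95% half-width for a share of 50%, ignoring clustering, is 1.96 × √(0.25/m) for m abortions.

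| | Relations only, 1,500 | Relations only, 2,000 | Stated yield |
|---|---|---|---|
| Kaya | ±9.8 points (m = 99) | ±8.5 (m = 132) | ±8.0 (m = 150) |
| Nairobi | ±6.7 points (m = 216) | ±5.8 (m = 288) | ±5.7 (m = 300) |

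**The case against.** The best defence is that the yield is right and an input was left out. The survey records respondents' own abortions, *Plans for analyses* describes their safety characteristics as well, and the sentence on the yield does not restrict itself to relations. Two relations plus the respondent make three women, and 148.5 and 324 fit the stated figures tolerably. The pre-test's secrets question also allows up to three women. This cannot be excluded. But the paragraph specifies "and two close relations" and ties the 50% to relations' abortions, and *Plans for analyses* treats self-reports as a separate analysis. *Background* says that direct questions get almost no response in many restrictive settings, so 50% for own abortions would need its own statement, although that remark is not about these two sites. On this defence too, the paragraph omits an input that it needs.

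A second objection concerns the inputs. The 22 per 1,000 is a rural rate, while *Phase 2: Main survey* says that the Kaya site has urban parts. A higher rate there could lift the Kaya yield, but it would not rescue Nairobi.

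Three stronger conclusions that a reader might draw are not supported:

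- **That 2,000 gives no margin at all.** It adds one third to whatever 1,500 yields. What is missing is a reserve over 150/300, and only if two relations are all that count. With three women per respondent, 198 and 432 would be a real reserve.
- **That the Kaya results will rest on a third fewer abortions than stated.** That compares 99 with 150 at 1,500 women. The plan interviews 2,000, where the gap is 12%.
- **That the profiles by sociodemographic category are undermined.** The abstract makes them conditional on success, and they also draw on the RDS, with up to 500 participants per site.

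**Conclusion.** The stated yield is wrong as written. The listed inputs give about 99 and 216 reported abortions at 1,500 women, and about 132 and 288 at the planned 2,000. The latter are 12% and 4% short of what the paragraph credits to 1,500. Whether the fault is the yield or an undeclared third woman per respondent cannot be settled from the article; either way the paragraph needs correcting.

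The practical effect at 2,000 is modest: about half a point of half-width in Kaya and a tenth of a point in Nairobi. The survey is descriptive, and the article states no precision target that would be missed.

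The conclusion assumes annual rates, the 3-year window, the rural rate for the whole Kaya site, and that every abortion of a close relation is known to the respondent, since the 50% is defined among women who know. The half-widths ignore clustering of relations within respondents.

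**What to change.** In *Sampling, inclusion criteria, and interview setting*, state the time unit of the rates, the 3-year window and the number of women counted per respondent. Then restate the yield at both sample sizes:

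- **If only two relations count:** give 99 and 216 at 1,500, and 132 and 288 at 2,000. Add the half-widths at 2,000 of about ±8.5 points (Kaya) and ±5.8 points (Nairobi) for a 50% share, ignoring clustering. Drop the implication that 2,000 is a reserve over 150/300.
- **If own abortions or a third relation count:** add that input with its own reporting rate and give the matching figures. At 50% these are about 149 and 324 at 1,500, and 198 and 432 at 2,000.

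The cost is rewriting one paragraph, with no extra interviews. The downside, on the two-relations reading, is a less favourable stated yield.

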##### Questionnaire

The questionnaire will include five sections.Sociodemographic characteristics and reproductive history of the respondent (including questions on her own abortions, towards the end of the interview).List of close network members, only females aged 15–49, with a standard network generator question from international social surveys and the shared secret question. Special care will be given to train fieldworkers and monitor them when administering this section, as interviewer effects have been identified in the literature for network generating questions.Characteristics of network members: sociodemographic characteristics (including whether in the area or not, since when in the area and since when a close relation), reproductive history, number and timing of any induced abortions in the past 3 years, how the abortion was induced (provider, setting, method), gestational age, post-abortion complications, treatment obtained for post-abortion complications, abortion related stigma, number of close relations by confidants. To maintain confidentiality, we will not collect information on relations' names but will ask them to provide nicknames or fictional names for each.Measures of abortion related stigma at the community level, personal level and internalized.

### Data collection: respondent-driven sampling

#### Recruitment, inclusion criteria and interview setting

When the ATPR is done, a different team of fieldworkers will start the RDS. To begin the RDS sample in the HDSS area, following the tested procedures, we will purposively select a sample of 8 to 12 women who reside in the area and have had abortions in the last 3 years as seeds to recruit our target population; they will be selected to represent the demographic, economic, residential and occupational diversity of the sites (see section on ethics in the discussion for details on seed recruitment). After providing informed consent, each seed will be interviewed face-to-face and provided with 3 coupons to recruit their peers who should meet the same inclusion criteria (reside in the site and have had an abortion, or in a multiplex design, reside in the site, and be close to someone who has had an abortion; pilot results will determine in which circumstances to recruit a social referent). Three coupons are given based on previous studies to avoid recruitment chains dying off at the beginning due to attrition. Coupons will be coded with a unique ID number so that recruiters can be linked to their recruits. They will also contain a phone number to call with enquiries, activation and expiry date. The research assistant will be allowed to join the respondent at the place the latter finds convenient for the interview; the interviewer will make sure the proposed place meets all confidentiality and privacy criteria before starting.

As in all RDS studies, each participant will receive two compensations (to be determined in accordance with local practices and national ethics committees, i.e. phone credits and/or travel expenses) for each successfully recruited additional participant. According to Heckathorn 1997, these rewards are more symbolic than substantive with studies showing that secondary compensation is particularly effective in facilitating the peer/social pressure needed to secure compliance to participate in studies within RDS networks. When participants return to the field office to receive their secondary compensation for recruiting participants, they will complete a questionnaire addressing if they tried to give coupons to other women who refused to accept it and why they were declined. All new recruits will be screened for eligibility to participate in the study after which informed consent will be taken and the questionnaire administered. They will then be trained to recruit other women and provided with coupons. The sample sizes of the RDS will be determined either during fieldwork, if saturation is reached and new respondents' characteristics are independent of those of the initial seed, or when the sample reaches a maximum of 500.

##### Questionnaire

The questionnaire administered to RDS participants will include:Sociodemographic characteristics and reproductive history of the respondent.Abortion history including number and timing of any induced abortions, how the abortion was induced (provider, setting, method), gestational age, post-abortion complications, treatment obtained, stigma (to be skipped for non-abortion seekers in multiplex RDS)Questions to estimate the biases of the ATPR: apply the ATPR modules to count close relations, characteristics of close relations, whether they had abortions, whether they told the respondents, how it was induced and any medical sequelae. For abortion seekers the module also contains the following questions: whether these close relations know about their abortions (whether respondents told them directly, respondents suspect they know even when not told).Stigma: three stigma scales will be used: community level, personal attitudes and internalized.

